# Treating Acute *EX*acerbations of *C*OPD with Chinese Herb*AL* Med*I*cine to aid Anti*B*iotic *U*se *R*eduction (EXCALIBUR): study protocol of a randomised double-blind, placebo-controlled feasibility trial

**DOI:** 10.1186/s40814-022-01224-8

**Published:** 2022-12-19

**Keywords:** Herbal medicine, Exacerbation, Chronic obstructive pulmonary disease, Randomised controlled trial, Feasibility, Qualitative

## Abstract

**Background:**

Acute exacerbations of chronic obstructive pulmonary disease (AECOPD) are a major reason for consultations in primary care, hospital admissions, deterioration in function, and mortality. Despite the majority of exacerbations not being caused by bacteria, as many as 70% of patients who present in UK primary care with AECOPD are prescribed antibiotics as part of standard care. However, finding effective non-antibiotic treatments for COPD exacerbations is a priority to reduce antibiotic use. The Chinese herbal medicine Shufeng Jiedu® (SFJD) has the potential to reduce treatment failure and duration of hospital stay. This study aims to determine the feasibility of conducting a fully powered randomised, double blind, placebo-controlled clinical trial on SFJD for AECOPD in UK primary care.

**Methods:**

This study is a phase III, two-arm individually double blind, randomised, placebo-controlled feasibility trial with nested qualitative study, coordinated by the Southampton Clinical Trial Unit (SCTU). Patients aged ≥ 40 years, with a current AECOPD, presenting with increased sputum purulence/volume, or breathlessness, and for whom the GP is considering use of antibiotics, will be eligible to participate. We aim to recruit seven eligible participants per month and randomise them to receive either the patent Chinese herbal medicine SFJD capsules or placebo for 14 consecutive days and to follow-up for 12 weeks. The primary outcomes include the feasibility of recruitment, study retention, and the percentage of diary completion.

**Discussion:**

If this trial demonstrates the feasibility of recruitment, delivery, and follow-up, we will seek funding for a fully powered placebo-controlled trial of SFJD for the treatment of AECOPD in primary care.

**Trial registration:**

This trial is registered via ISRCTN on 1 July 2021, identifier: ISRCTN26614726.

**Supplementary Information:**

The online version contains supplementary material available at 10.1186/s40814-022-01224-8.

## Background

Chronic obstructive pulmonary disease (COPD) is a common, preventable, and treatable condition that is characterised by persistent respiratory symptoms and airflow limitation [1]. The point prevalence of COPD was estimated to be 3.92% (95% CI 3.52–4.32%) worldwide in 2017 [2]. In the UK, there are an estimated 3 million people with COPD [3], with approximately 1.17 million people diagnosed, representing 1.9% of the population [4].

COPD is a leading cause of morbidity and mortality, associated with significant economic burden. Due to its nature as a chronic disease, patients typically have an impaired quality of life and suffer from disability and impaired motility. As the third leading cause of death worldwide [5], COPD accounts for 5.72% of all-cause deaths with an estimated disability-adjusted life years (DALYs) rate at 1068/100,000 [2]. In the UK, COPD is estimated to result in around 1.4 million GP consultations and 130,000 emergency hospital admissions, with a direct cost to the NHS of £810–£930 million annually [6]. Current global projections indicate that COPD is set to increase in line with ageing populations. It is predicted to increase from causing 3 million deaths annually in 2010 [7] to 5.4 million deaths annually by 2060 [8].

Acute exacerbations of COPD (AECOPD) are acute worsening of respiratory symptoms that require additional therapy [1]. They are major reasons for deterioration in function and mortality, accounting for a large proportion of healthcare costs. Further economic impact is driven by loss of working days due to illness. Standard care of acute exacerbations includes antibiotics, and 70% of patients presenting with AECOPD in UK primary care are currently in receipt of antibiotics [9]. The most common causes of the exacerbations are bacterial infections, viral infections, and environmental triggers, with 49.6% (95% CI: 44.2–55.0) being triggered by bacterial infection [10] and 37.4% (95% CI: 35.9–38.8) by viral infection [11]. Antibiotics are sometimes used inappropriately in AECOPD and could be potentially reduced [12]. Patients with COPD are particularly at risk of antibiotic-resistant infections, as they may receive multiple courses and excessive use of antibiotics [13, 14].

Strategies to better target antibiotics can safely reduce prescribing [9]. Antimicrobial treatment in patients with COPD can reduce the infecting load without entirely eradicating organisms in the airways, leading to an increased risk of resistant bacteria [15]. Finding effective non-antibiotic treatments for COPD exacerbations is a priority to reduce antibiotic use.

Traditional herbal medicines have the potential to improve symptoms of acute respiratory tract infections [16–19] and hence reduce both the symptom burden of these illnesses and unnecessary antibiotic prescribing both nationally and internationally. The Chinese herbal medicine Shufeng Jiedu® (SFJD) capsule is a patent formula consisting of eight Chinese herbs, all of which are used traditionally for treating respiratory infections (Table 1). SFJD is already on the market in China for treating respiratory conditions, with promising evidence showing its effects in various acute upper RTIs [20] and community-acquired pneumonia [21].

**Table 1 Tab1:** Composition of SFJD

Functional roles^1^	Botanical species	Common names and plant part	Pin Yin^1^	Amount (g)	Cultivated from
Sovereign	*Fallopia japonica* [22]	Japanese Knotweed, *rhizome*	Hu Zhang	0.45	Lu’an, Anhui
Minister	*Forsythia suspensa*	Weeping Forsythia, *fruit*	Lian Qiao	0.36	Yuncheng, Shanxi
	*Isatis indigotica*	Indigo Woad, *root*	Ban Lan Gen	0.36	Tsitsihar, Heilongjiang
Assistant	*Bupleurum chinense* [23]	Chinese thoroughwax, *root*	Chai Hu	0.36	Weinan, Shaanxi
	*Patrinia scabiosaefolia*	Yellow Flowered Valerian, *herb*	Bai Jiang Cao	0.36	Enshi, Hubei
	*Verbena officinalis*	Vervain, *herb*	Ma Bian Cao	0.36	Xiangyang, Hubei
	*Phragmites communis*	Reed, *rhizome*	Lu Gen	0.27	Anguo, Hebei
Envoy	*Glycyrrhiza uralensis*	Liquorice, *root*	Gan Cao	0.18	Dingxi, Gansu

^1^The prescription of SFJD following the basic principle of Chinese herbal medicine formulation, sovereign, minister, assistant, and envoy [君臣佐使] principle, where sovereign herb plays a major role in providing treatment effects for the main syndrome/symptom; minister herbs assist the sovereign herb to strengthen treatment effects and to treat the concurrent syndrome/symptom; assistant herbs assist the sovereign and minister herbs to strengthen the therapeutic effects, treat the secondary syndrome/symptom, or reduce the side effects of sovereign and minister herbs that may have; and envoy herb deliver the other herbs to the right place in the body [24]

A systematic review of randomised controlled trials has shown that when added to usual care for AECOPD, SFJD reduces treatment failure from 20.1 to 8.3% (11 trials; 815 patients; relative risk 0.43, 95% confidence interval [CI] 0.30 to 0.62; low certainty) and duration of hospital stay (2 trials; 79 patients; mean difference − 4.35 days, 95% CI − 5.28 to − 3.43 days), compared with usual care alone in Chinese population [25]. A comprehensive synthesis of evidence regarding SFJD safety identified no serious adverse events from clinical trials or pharmacovigilance data [26]. Minor adverse events included nausea/vomiting, diarrhoea, unspecified gastrointestinal discomfort, dizziness, and rash; however, these were not statistically significantly different to control groups. No substantive safety concerns were identified for SFJD for clinical use, excluding pregnant or lactating women [26].

Based on these studies, we hypothesise that SFJD may improve symptoms in people with AECOPD and therefore reduce the necessity for antibiotics, the risk and duration of admission to hospital, and the risk of relapse.

This study aims to determine the feasibility of conducting a fully powered randomised controlled trial of SFJD in addition to usual care for AECOPD in UK primary care. Specific objectives are to test feasibility of trial recruitment process and retention, intervention management and procedures, and collecting outcome measures. We will also explore participants’ experiences of the trial procedures and their views of taking SFJD for their AECOPD.

## Methods

### Study design

The EXCALIBUR study is a double-blind, randomised placebo-controlled feasibility trial (ISRCTN26614726) [27]. This trial protocol has received the favourable opinion of a Research Ethics Committee or Institutional Review Board (IRB) in the approved national participating countries (IRAS number 268737, Appendix 1; sponsor reference number 47948, Appendix 2; Ethical approval: REC reference 20/LO/0580, Appendix 3). A nested qualitative study will be undertaken with patients, including both those who agreed and declined to participate in EXCALIBUR (Fig. 1).

**Fig. 1 Fig1:**
[figure not shown]
Trial schema

This protocol provides details for the study following the Standard Protocol Items for Clinical Trials (SPIRIT) 2013 statement [28] (Appendix 4). The final study results will be reported following the CONSORT Extension for Chinese Herbal Medicine Formulas [29], with the nested qualitative elements being reported using the COREQ checklist [30].

### Setting of the study

The study will be conducted in eight general practices in the Wessex region of the United Kingdom, coordinated by the Southampton Clinical Trial Unit (SCTU).

### Participants

The study selection criteria are outlined below. Patient eligibility to take part in the EXCALIBUR trial will be confirmed by a qualified GP or Nurse Prescriber. Evidence of eligibility criteria will be documented in the patient’s medical or research notes.

#### Inclusion criteria

Patients who fulfil all the following criteria will be recruited.Has a current acute exacerbation of COPD with at least one of the following:Increased sputum purulenceIncreased sputum volumeIncreased breathlessnessThe current acute exacerbation has lasted for at least 24 hours and no longer than 21 daysThe responsible clinician is considering use of antibiotics for the acute exacerbationDiagnosis of COPD in clinical recordAge 40 years or moreAble to provide informed consentAble to provide the primary outcome data at 2 and 4 weeks

#### Exclusion criteria

The responsible clinician feels urgent referral to hospital is necessarySevere illness, e.g. suspected pneumonia or pulmonary embolism or lung cancer; necessity for emergency admission to hospitalPatient has a primary diagnosis of bronchiectasis, lung cancer or other active chronic respiratory diseaseCurrently on or has previously had antibiotics or corticosteroids for this episode of AECOPDPatient is on a maintenance dose of antibiotics for treatment of COPDKnown or suspected pregnancyWomen of childbearing potential who are at risk of pregnancy and not using an effective form of contraceptionCurrently breast-feedingChronic kidney disease stage 4 or 5Severe liver diseaseCannot read or understand the study materialsPreviously recruited into this ‘EXCALIBUR’ trialPreviously recruited into another drug trial within the last 6 weeks

### Sample size

The target sample size for this trial is 80 patients (40 per arm), which means recruiting seven eligible participants per month. Patients will receive either SFJD or placebo capsules in 1:1 allocation ratio.

As this is a feasibility trial, no formal sample size calculation was carried out. However, using a 95% confidence interval approach and conservatively assuming a 50% participation rate (to give the worst-case scenario), it can be shown that this sample size allows us to predict the recruitment rate to within ± 13% [IBM SPSS Statistics for Macintosh, Version 25.0].

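### The ±13% precision stated for the recruitment rate does not follow from its inputs: it is about ±11 points on 80 patients, and about ±8 points on the eligible-patient denominator

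*Protocol article*

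**What the plan says.** The Sample size section sets the size first: "The target sample size for this trial is 80 patients (40 per arm"). It then disclaims a formal derivation: "As this is a feasibility trial, no formal sample size calculation was carried out". It goes on to say what 80 would deliver. "using a 95% confidence interval approach" and "conservatively assuming a 50% participation rate (to give the worst-case scenario"), it concludes that "it can be shown that this sample size allows us to predict the recruitment rate to within" ±13%. So the confidence level, the assumed proportion, the number of patients and the result all stand in one short paragraph.

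The section Outcome measurements and data collection, under recruitment process and retention, defines the recruitment proportion as the share of eligible patients who are recruited or randomised. It lists the monthly recruitment rate as a separate item. The abstract names the quantities of main interest: "The primary outcomes include the feasibility of recruitment, study retention, and the percentage of diary completion". The ±13% for recruitment is the only precision figure that the article gives for any of the trial's own endpoints.

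**The concern.** Two things look wrong. First, the half-width of a 95% interval for a proportion of 50% on 80 people is a one-line calculation, and it does not give 13 points. Second, the 80 are the patients who will have been randomised. For a proportion of eligible patients recruited they are the top of the fraction, not the bottom, so correcting 13 to 11 would still leave the sentence wrong for the quantity it names.

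The purpose of the trial is estimation, and the step to a full trial depends on how well feasibility is known. A precision statement that cannot be reproduced, with no denominator named, may be carried into the planning of that trial or applied to endpoints for which it was not meant.

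**Working it through.** **Inputs, all from the protocol article.** Target n = 80, 40 per arm (Sample size); 95% two-sided interval (Sample size); p = 0.50 (Sample size); stated half-width 13 percentage points (Sample size); recruitment proportion = recruited ÷ eligible (Outcome measurements and data collection).

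**Step 1: attempt to reproduce the stated figure.** Wald half-width = z × √(p(1 − p)/n).

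1.96 × √(0.5 × 0.5 / 80) = 1.96 × 0.0559 = 0.1096, that is ±11.0 points.

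Other 95% methods at n = 80, p = 0.5:

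| Method | Half-width (points) |
|---|---|
| Wilson | 10.7 |
| Agresti-Coull | 10.7 |
| Wald | 11.0 |
| t-based | 11.2 |
| Exact (Clopper-Pearson) | 11.4 |
| Wald with continuity correction | 11.6 |

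None rounds to 13. The stated figure is not reproduced.

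**Step 2: what would give 13?**

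- Solving for n at 95%: 1.96² × 0.25 / 0.13² = 56.8, so about 57 people (53 to 61 for any half-width that rounds to 13).
- Starting from 80, that means a loss of roughly 25% to 30% (n = 60: 12.7; n = 56: 13.1). The section states no such allowance.
- At n = 80, a 98% interval gives 13.0, but the text says 95%.
- One arm of 40 gives 15.5.

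The 57 people and the 98% level are arithmetic matches only. The document supports neither as the source.

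**Step 3: use the denominator that the endpoint definition gives.** At 50% participation, 80 recruited implies 80 / 0.5 = 160 eligible.

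1.96 × √(0.25 / 160) = 1.96 × 0.0395 = 0.0775, that is ±7.7 points; the exact interval gives ±8.0.

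For other assumed participation rates with 80 recruited (Wald): 30% means about 267 eligible and ±5.5; 70% means about 114 eligible and ±8.4.

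**Step 4: proportions that do have the 80 as denominator.** For retention or diary return the largest half-width is the ±11.0 of Step 1. At an assumed 80% it is 1.96 × √(0.8 × 0.2 / 80) = ±8.8, and at an assumed 90% it is ±6.6.

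**The case against.** The best defence is that the error is harmless. Both recomputed half-widths, 11.0 and 7.7, are smaller than 13, so a claim of precision to within ±13% is literally met. The article says that no formal calculation was made, the analysis is descriptive, and the reported intervals will come from observed data. The Trial status section also says that recruitment is already complete. All of this stands, and it limits the weight of the point. It does not make the printed figure correct: the inputs and the result stand together and do not agree, which neither condensation of a longer protocol nor a separate analysis plan explains.

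Some stronger readings are tempting, but the documents do not support them.

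- *The stated precision is wrong for every endpoint.* A precision is stated for one quantity only. Retention and diary completion have no stated figure that could be wrong, and the absence of one, overall or per arm, is detail that may sit in the full protocol or analysis plan. The per-arm ±15.5 has no bearing on recruitment, which precedes allocation.
- *Eighty is too few.* Nothing here shows that.
- *50% is not the worst case.* This holds only if sampling stops at exactly 80 recruited. The article calls 80 a target and closes recruitment by a calendar limit before the last visit. The difference is in any case small (8.4 at 70% against 7.7 at 50%).
- *The figure should be an interval for the monthly rate.* The sentence assumes a participation proportion, and a count-based interval would need a recruitment period that the Sample size section does not state.
- *Clustering explains or undoes the result.* The section mentions no clustering, and no intracluster correlation is given. If one assumes eight equal practices with 20 eligible each (160 / 8), the half-width is 7.75 × √(1 + 19 × ICC): 9.1 at an assumed ICC of 0.02, 10.8 at 0.05 and 13.2 at 0.10. That range is a reason to attach a caveat to the ±8. It cannot be read as the origin of the 13. Equal clusters are themselves uncertain, since patients may also come from other practices in the same network.

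**Conclusion.** The point holds as a minor correction. On the section's own inputs the half-width is about ±11 points, not ±13. For the recruitment proportion as the article defines it, the denominator at 50% participation is about 160, and the half-width is about ±8 points. The overstatement is therefore about 2 points on the first basis (13 − 11.0) and about 5 on the second (13 − 7.7 = 5.3 Wald, 13 − 8.0 = 5.0 exact).

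The ±8 rests on the article's 50% participation, on the target of 80 being met, and on independent patients with no practice effect. Under those assumptions the printed figure errs on the cautious side. How the 13 arose cannot be told from the document.

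**What to change.** Replace the ±13% sentence with one that names its denominator, for example:

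> A 50% participation rate (80 of about 160 eligible) would be estimated to within about ±8 percentage points, before any allowance for clustering by practice; a proportion of the 80 randomised, such as retention, to within at most about ±11 percentage points.

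The worst-case label then belongs with the second clause, where 80 is a fixed denominator. If the ±13% came from an input that the article does not show, such as an allowance for loss, state that input instead and give the calculation.

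The cost is one sentence, with no change to sample size, conduct or analysis. As recruitment has ended, the practical places to make the correction are the results report and any planning document for the full trial that would otherwise cite the ±13%.

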### Recruitment and consent

As clinical care has not yet returned to pre-pandemic patterns, both face-to-face and remote recruitment will be carried out.

Potential participants will be identified in several ways:Participating practices will search their electronic records for patients on their COPD register and flag those who suffered one or more exacerbations in the last 5 years. These patients will then receive a mailed trial introduction pack to allow them to easily identify themselves when they contact the surgery.Patients who fulfil this criterion at other practices in the participating practice’s Primary Care Network (PCN) may also be contacted and informed about the trial.Participating practices may screen and recruit AECOPD patients who present opportunistically at their practice or at practices in their PCN.Advertisement through trial posters in surgery waiting areas.Practices will advertise the trial on platforms such as practice websites and social media accounts.

Potentially eligible patients will be sent an invitation letter by Docmail informing them about the study, a summary participant information sheet (PIS), and a patient card with ‘potentially eligible for EXCALIBUR Trial’. Participating clinicians will be asked to approach potentially eligible patients opportunistically in triage sessions. The GP will initially assess the patient and make a clinical decision on treatment as per standard care. Should the patient be deemed potentially eligible for the EXCALIBUR trial, they will be provided with a PIS and if the patient recruitment process is being conducted remotely a link to the trial consent website containing an electronic PIS. They will be allowed sufficient time to decide whether to participate and ask any questions they may have.

Informed consent will be taken face-to-face or through the trial consent website using a bespoke e-consent platform. The right of the patient to refuse to participate without giving reasons will be respected. All participants will be free to withdraw from the trial at any time without providing reasons and without prejudicing further treatment. Participants in the trial who are potentially interested in being interviewed will be asked for consent to share their contact details with the qualitative researcher. PIS and consent form are available in Appendix 5.

Following explicit consent from the participant to do so, participant details will be collected on the trial website for the purpose of conducting the trial. For randomised participants who are recruited remotely, the trial medication and participant diaries/questionnaires will be delivered to their home address via dedicated courier.

### Confidentiality

SCTU will preserve the confidentiality of participants taking part in the trial. The investigator must ensure that participants’ anonymity will be maintained and that their identities are protected from unauthorised parties. On CRFs participants will not be identified by their names, but by an identification code. For the qualitative aspects of the study, transcripts will be anonymised before analysis.

### Randomisation

Eligible participants who have provided written or online informed consent will be individually randomised in a 1:1 allocation ratio to receive SFJD or placebo treatment. The randomisation sequence was generated using block randomisation with no stratification factors with Stata version 16.0 (StataCorp LLC) by a statistician [KT] at the SCTU. Randomisation codes were securely sent by the statistician [KT] to a labelling and packaging (design approved by the study sponsor) technician at Anhui Jiren Pharmaceutical Co., Ltd. China, who was not involved in the administration of the trial. Once a patient has been randomised, the recruiting site will inform the SCTU by scanning and emailing through the eligibility-randomisation form within 24 h of randomisation.

The treatment packs are sent to site in sets of four and each patient will receive the next available sequentially numbered patient pack at their site. This will determine their patient identifier number. The doctor or nurse allocating the patient pack and the patient will not know to which treatment arm they have been randomised. The patient pack will contain either SFJD or placebo capsules. Outcome assessors will also be blind to treatment allocation.

